#### Strategies to Improve Adherence to Interventions

To promote engagement and adherence, participants in the experimental group will receive up to 6 one-to-one online video sessions with a trained female therapist, which introduces a human element that reinforces the therapeutic relationship and strengthens the therapeutic alliance. Additionally, time-sensitive notifications will be used to prompt participants when prescribed modules or worksheets remain incomplete. These automated reminders are designed to support program adherence, self-monitoring, and sustained participation throughout the intervention.

#### Relevant Concomitant Care Permitted or Prohibited During the Trial

Pharmacological treatment will be permitted, provided it was initiated at least 1 month before study entry. Concomitant pharmacotherapy (agent and dose) will be recorded at baseline, tracked for changes during subsequent assessments, and compared between the groups after randomization to detect any imbalances. Any concurrent psychological interventions or psychological care will not be permitted during the trial period to avoid confounding effects. Should any intensification of clinical care become necessary during the trial—including psychological interventions, changes to pharmacotherapy, specialist referrals, or crisis interventions—it will be documented in the trial log as part of the adverse event monitoring procedure. Where these intensifications reflect clinically significant symptoms worsening requiring alternate or intensive care, the participant may be discontinued from the trial in consultation with their treating team (see the *Criteria for Discontinuing or Modifying Allocated Interventions* section).

### Assignment of Interventions

#### Randomization

Participants will be randomized in a 1:1 ratio using the REDCap randomization module, which will automatically assign participants to either the experimental group or control group through simple randomization with equal allocation. The allocation sequence will be generated by an independent statistician or REDCap administrator who is not involved in participant recruitment, outcome assessment, or data analysis using the National Cancer Institute (NCI) Clinical Trial Randomization Tool [22]. This individual will be responsible for uploading the allocation table to REDCap, ensuring that allocation concealment is maintained throughout enrollment.

Following randomization, a designated unblinded team member (eg, intervention therapists) will access the group assignment in REDCap and will be responsible for providing participants with access credentials and instructions for the appropriate version of the intervention platform, according to their assigned group.

#### Blinding

This is a single-blind trial. Due to the nature of the intervention, participants will be aware of their group assignment after randomization. Likewise, therapists delivering the intervention will not be blinded, as is standard in psychological trials. To preserve blinding where possible and minimize bias, the following measures will be implemented: (1) outcome assessors will remain blinded to group allocation and will not have access to REDCap fields containing the randomization result; (2) data analysts will be blinded during analyses; and (3) all other stakeholders, including clinicians, statisticians, laboratory analysts, and the principal investigator, will not have access to group assignment information or the randomization sequence. Access control within REDCap will be configured using role-based permissions to ensure that only designated unblinded personnel can view or export the group allocation information.

### Data Collection

#### Overview

Data will be stored on a secure server at the Hospital del Mar Research Institute (HMRI), in compliance with EU and Spanish data protection regulations, namely the General Data Protection Regulation (GDPR) of May 25, 2018, and Organic Law 3/2018 of December 5, on the Protection of Personal Data and the Guarantee of Digital Rights.

#### Procedure

Assessments will be conducted at 3 time points: baseline (T0), postintervention (12 weeks after baseline, T1), and follow-up (26 weeks after baseline, T2).

The baseline assessment will include the collection of sociodemographic and clinical data, the administration of primary and secondary outcome measures, a gynecological consultation to assess hormonal and menstrual health, and the collection of biological samples.

At T1 and T2, follow-up assessments will include the administration of primary and secondary outcome measures as well as biological sample collection.

All psychological assessments will be carried out by a trained professional (psychologist, physician, psychiatrist, or psychiatric nurse), gynecological examinations will be performed by a licensed gynecologist (MD in obstetrics and gynecology), and biological samples will be collected by a registered nurse. Participant timeline, including the schedule of enrollment, interventions, and assessments, is outlined in Table 1. All professionals with direct participant contact—whether via teleconference or in-person—will be women. This decision was reached by consensus within the focus group of women with a lived experience of depression, who expressed that sensitive topics (eg, hormonal changes, gender discrimination, and sexuality in the context of depression) would be better understood by female professionals and that participants would feel more comfortable accordingly.

**Table 1. T1:** SPIRIT (Standard Protocol Items: Recommendations for Interventional Trials) participant timeline.

Study procedure	Trial period					
	Preintervention			Intervention	Postintervention	Follow-up
Time point	–t0	T0	T0	—^a^	T1	T2
Weeks	0	1	2	3‐12	12	26
Enrollment						
Eligibility screen	*✓*					
Informed consent		✓				
Inclusion		✓				
Randomization		✓				
Interventions						
Intervention (3D Program)				✓		
Control group (informational videos)				✓		
Screening assessments						
Sociodemographic information		✓				
Medical and psychiatric history		✓				
Gynecological visit			✓			
Primary outcome						
HDRS-17^b^		✓			✓	✓
Secondary outcomes						
WHODAS 2.0^c^		✓			✓	✓
EQ-5D-5L^d^		✓			✓	✓
PSS^e^** **		✓			✓	✓
MEDI-Q^f^** **		✓			✓	✓
Biological samples						
Plasma			✓		✓	✓
Saliva			✓		✓	✓
Urine			✓		✓	✓
Nails			✓		✓	✓
Hair			✓		✓	✓

a Not applicable.

b HDRS-17: 17-item Hamilton Depression Rating Scale.

c WHODAS 2.0: World Health Organization Disability Assessment Schedule 2.0 (36-item version).

d EQ-5D-5L: EuroQol 5-Dimension 5-Level.

e PSS: Perceived Stress Scale.

f MEDI-Q: Menstrual Distress Questionnaire.

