#### Eligibility

Eligible participants will be women (including both cisgender and transgender) aged 18 to 45 years (inclusive) who present with moderate depressive symptoms at baseline, defined as a score of 17 to 23 on the 17-item Hamilton Depression Rating Scale (HDRS-17). Additional inclusion criteria are fluency in Catalan or Spanish, regular internet access, and the ability to independently use a digital device (eg, smartphone, tablet, or computer).

Participants will be excluded if they are currently receiving psychological therapy, as concurrent structured psychotherapy would confound the estimation of the 3D Program’s effect; have participated in another interventional clinical trial for depression in the past 3 months; are pregnant or planning to become pregnant during the study period, given the distinctiveness of perinatal depression and because pregnancy-related hormonal fluctuations would confound the exploratory biomarker analyses; have cognitive impairment that would interfere with informed consent or study participation; or currently present with psychotic symptoms, active suicidal ideation, or substance use disorder. Women older than 45 years will be excluded to minimize potential confounding effects of perimenopausal hormonal changes. Participants with severe depression will be excluded due to safety considerations, as this population requires more intensive, closely monitored treatment than the 3D Program is designed to provide.

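### Table 1 randomizes women in week 1 but takes the baseline gynecological visit and all baseline samples in week 2, when they may already know their arm

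*Protocol article*

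**What the plan says.** Under Data Collection, Procedure, the article lists what belongs to baseline (T0). Besides sociodemographic and clinical data and the outcome measures, this includes "a gynecological consultation to assess hormonal and menstrual health, and the collection of biological samples".

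Table 1, in the same section, splits T0 into two columns, week 1 and week 2. Consent, inclusion, randomization, the HDRS-17 and the four questionnaires are ticked in week 1. The row "Gynecological visit" and the rows for plasma, saliva, urine, nails and hair are ticked in week 2. The intervention occupies weeks 3 to 12.

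On knowledge of the arm, the Blinding section says "participants will be aware of their group assignment after randomization". The Randomization section says that, once randomization has taken place, an unblinded team member "will be responsible for providing participants with access credentials and instructions for the appropriate version of the intervention platform". Neither section gives a day, and neither makes disclosure wait for the second T0 visit.

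**The concern.** A baseline value serves as a predictor, moderator or covariate because it was fixed before allocation could influence it. If a woman learns her arm and only then attends the visit at which the value is obtained, two things can vary with the arm: whether the value exists at all, and how carefully the specimen was collected.

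Three parts of the plan depend on this not happening:

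- The Missing Data section runs the cluster and factor analyses without imputation. It says that they use baseline data only and that the gaps will be few and unrelated to anything systematic.
- The Predictors and Covariate Analysis section looks for baseline predictors of improvement, and the Discussion presents sex hormones and glucocorticoids as possible moderators of the treatment effect.
- BMI, listed as an additional variable under Participant Characteristics and Clinical Data, comes from weight and height taken at the gynecological visit.

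**Working it through.** **1. The plan's own design figure.** The Sample Size Calculation section gives f = 0.15, α = .05, power 0.90, correlation 0.5, ε = 1, 2 groups and 3 measurements. For the group-by-time interaction:

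- λ = f²·N·m/(1−ρ) = 0.0225 × 96 × 3 / 0.5 = 12.96
- df1 = (2−1)(3−1) = 2 and df2 = (96−2) × 2 = 188
- power at N = 96 is 0.902; at N = 94 it is 0.896
- 96/(1−0.20) = 120

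Both 96 and 120 reproduce. The point below does not depend on them. They matter only for showing what is not affected.

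**2. Order of events in Table 1.** Each tick was read against its week column.

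| Item | Column | Week |
|---|---|---|
| Eligibility screen | –t0 | 0 |
| Consent, inclusion, randomization | first T0 | 1 |
| Baseline HDRS-17 and questionnaires | first T0 | 1 |
| Gynecological visit (with BMI) | second T0 | 2 |
| Plasma, saliva, urine, nails, hair | second T0 | 2 |
| Intervention | – | 3–12 |

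The samples and the visit follow randomization by 2 − 1 = 1 column, nominally one week. They precede the start of treatment by 3 − 2 = 1 week. The HDRS-17 and the questionnaires share the week-1 column with randomization. The table does not show the order within that week, and no point is made of it here.

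**3. Who knows the arm in week 2.** The Blinding section makes participants and therapists aware of allocation and keeps outcome assessors, clinicians, laboratory analysts and data analysts unaware. The Randomization section places arm-specific instructions after randomization. Read with Table 1, a woman may know her arm at the second T0 visit. No sentence rules this out.

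**4. Where her knowledge can act.** The laboratory is not the route, because it is blinded. Two routes remain:

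- *Attendance.* All five matrices are collected or delivered at the visit, and BMI is measured there.
- *Home collection.* Under Sample Types and Collection Procedures, three of the five matrices (urine, saliva, nails) are collected by the woman herself beforehand. The Discussion accepts that this relies on her compliance.

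**5. A related mismatch in the same table.** The text sets T1 and T2 at 12 and 26 weeks after baseline. On Table 1's week numbers, T1 falls 12 − 1 = 11 weeks after the HDRS-17 and 12 − 2 = 10 weeks after the samples. T2 falls 25 and 24 weeks after them. Any correction of Table 1 should settle this too.

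**The case against.** The strongest reply is that the consequences are small and partly inferred. Much of it stands.

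- *Disclosure is not dated.* The article ties it to randomization without giving a day, and the platform is not needed until week 3, so the team may in practice tell women late. That would shrink the problem, but the article does not say so.
- *The data are exploratory.* The Analytical Methods section calls the biomarker work hypothesis-generating and unpowered, samples precede treatment, and the laboratory is blinded. All true, and this limits the weight of the point. An exploratory analysis still needs a clean baseline if it is to suggest predictors or moderators.
- *Multiple imputation* is planned for the multiple regression and partial least squares models. It could absorb missingness that depends on arm if arm is in the imputation model. It would not help the analyses run without imputation, nor correct a change in how specimens were collected.
- *Lower attendance by control women* is stated nowhere. What can be said is that the schedule permits a difference in either direction.

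Three stronger readings are tempting, and the document does not support them.

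- *That losses between weeks 1 and 2 use up the 120 − 96 = 24 women allowed for attrition.* A woman who misses the week-2 visit keeps her week-1 HDRS-17, can be assessed at T1 and T2, and stays in the intention-to-treat mixed model. A woman who leaves altogether is ordinary dropout, which the allowance is there to cover. The document gives no loss rate for this interval.
- *That ineligible women will be discovered after randomization,* because women who "are pregnant or planning to become pregnant during the study period" are excluded and reproductive history is taken in week 2. The eligibility screen is in week 0 and inclusion in week 1. The gynecological visit is not described as an eligibility gate, no pregnancy test is mentioned there, and abnormal findings lead to referral.
- *That women choose which samples to give once they know their arm.* The Informed Consent section places that choice within consent, which Table 1 lists before randomization.

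**Conclusion.** The point holds in a limited form. As scheduled, the gynecological data, including BMI, and all five baseline matrices are obtained after randomization, and the article lets participants know their arm by then. The assumption of unsystematic baseline missingness and the baseline biomarker, predictor and moderator analyses are therefore less secure than they need be. The primary HDRS-17 analysis and its power are unaffected, and treatment cannot contaminate the samples.

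No numerical size can be given, because the document offers no basis for the rate or direction of any difference between arms. The ceiling is 120 women. The true number will be lower wherever women decline some samples or are not cisgender, since only specimens from cisgender women are analyzed. The conclusion assumes that Table 1's columns mean what they say and that disclosure follows randomization without a hold. If the full protocol holds disclosure until week 2 is complete, only the wording needs correcting.

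**What to change.** Preferred: move randomization, and with it the release of credentials, to the end of the week-2 baseline visit, after the consultation and samples, and correct Table 1. The week-3 start and the number of visits stay as they are. The Randomization, Blinding and Procedure sections should then agree with the table, including the week numbers of T1 and T2.

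Minimum: keep randomization in week 1 and state that the arm is not disclosed to the participant until week-2 collection is complete. A woman who does not return for week 2 would still count as randomized without baseline samples, but her absence could not depend on knowing her arm.

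In either case, flag women already randomized under the present order in the biomarker analyses. The article reports 8 enrolled by April 2026, so at that date up to 120 − 8 = 112 women could still be enrolled under a corrected schedule.

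The cost is an amendment to the text and Table 1, with the REDCap workflow changed to match. The preferred option also leaves less time to issue credentials and set up therapists before week 3, and puts about one week between the qualifying HDRS-17 and randomization. The minimum option avoids the second of these.

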#### Primary Outcome Measures

Change in depressive symptoms from baseline (T0) to 12 weeks (T1) and 26 weeks (T2) was assessed using the clinician-administered HDRS-17, which was validated in Spanish [23,24]. The HDRS-17 total score ranges from 0 to 52, with higher scores indicating more severe depression.

#### Secondary Outcome Measures

Secondary outcomes will include changes from baseline (T0) to 12 weeks (T1) and 26 weeks (T2) in overall functioning, health-related quality of life, perceived stress, and menstruation-related distress.

Overall functioning: Assessed via the self-administered World Health Organization Disability Assessment Schedule 2.0 (WHODAS 2.0; 36-item version) [25,26]. It evaluates functioning across 6 domains, with higher scores indicating greater disability.Health-related quality of life: Measured by the self-reported EuroQol 5-Dimension 5-Level (EQ-5D-5L) [27,28], which assesses 5 dimensions of health on a 5-point scale. Responses are combined into a single index value ranging from below 0 (health states worse than death) to 1 (full health). A visual analogue scale is also included, ranging from 0 (worst imaginable health) to 100 (best imaginable health).Perceived stress: Evaluated using the self-reported Perceived Stress Scale (PSS) [29,30]. Items are rated on a 5-point Likert scale from 0 (never) to 4 (very often), yielding a total score from 0 to 56. Higher scores reflect greater perceived stress.Menstruation-related distress: Assessed via the 25-item self-reported Menstrual Distress Questionnaire (MEDI-Q) [31]. It evaluates symptoms such as pain, discomfort, psychological changes, gastrointestinal symptoms, and physiological alterations.

All instruments, except for the MEDI-Q, will be used in their Spanish validated versions. As the MEDI-Q is a recently developed tool not yet validated in Spanish, its use in this study provides an opportunity for initial cultural adaptation within this population.

### Biological Samples

#### Sample Types and Collection Procedures

Biological analysis will be conducted exclusively on specimens collected from cisgender women participants. Biological specimens to be collected include plasma, urine, saliva, fingernails, and hair. All collection procedures will adhere to standard operating procedures, with participant safety and comfort as priorities. Specific procedures for each biological sample are as follows:

Plasma: Blood samples will be collected using EDTA K2 plastic tubes (13 × 75 mm, 4 mL). Two tubes (totaling 8 mL) will be collected per participant on the day of the assessment visit.Urine: Participants will self-collect approximately 50 mL of midstream urine the night before their scheduled assessment visit, using a sterile 60-mL polypropylene container. The sample will be refrigerated overnight at the participant’s home and transported to the research facility on the day of the visit.Saliva: Participants will self-collect saliva samples the night before the assessment visit using 2 Salivette Cortisol collection devices. Samples will be refrigerated overnight at the participant’s home and transported to the research facility on the day of the visit.Fingernails: Participants will clip the distal ends of their fingernails at home before the assessment visit. Samples will be collected in sealed paper envelopes.Hair: A strand of hair (approximately 0.5 cm in diameter, or 50 mg for short hair) will be cut from the posterior vertex as close to the scalp as possible by trained personnel. The root end will be marked with a hair tie. Samples will be collected in sealed paper envelopes.

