#### Sample Processing Protocols

The collected biological samples will be processed according to standardized protocols prior to laboratory analysis, as outlined below:

Plasma, urine, and saliva: All samples will be centrifuged upon arrival at the laboratory. Aliquots will be prepared as necessary. Chemical treatment will be applied if specified in the manufacturer’s protocol for the collection device (eg, Salivette for saliva). All reprocessing procedures will follow the manufacturer’s instructions.Fingernail samples will be washed with an organic solvent to remove external contaminants, then dried and mechanically ground using a ball mill to produce a homogeneous powder suitable for downstream analysis.Hair samples will undergo solvent-based washing to remove surface contamination, followed by drying and mechanical pulverization using a ball mill to prepare for analytical procedures.

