#### Metabolomics

Partial least squares regression and multiple regression analyses will be used to model associations between metabolite profiles, their changes over time, and changes in depressive symptoms. Variable importance in projection scores and cross-validation techniques will be used to evaluate model performance and identify key predictive biomarkers. Additionally, metabolomic changes will be assessed through exploratory factor analysis, grouping variables into latent factors. It should be noted that the study was originally conceptualized and powered as a confirmatory superiority RCT; therefore, the metabolomics substudy should be considered secondary and may be limited by this design. Nevertheless, given the scarcity of data in this biological field of research, we believe it is worthwhile to conduct this post hoc exploratory proof-of-concept study.

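### Distal fingernail clippings at T1 formed essentially before baseline under plausible growth rates, so the T0-T1 nail change should not be related to the concurrent HDRS-17 change; the hair segment needs confirming

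*Protocol article*

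**What the plan says.** Protocol article, Procedure and Table 1: visits are at baseline, 12 weeks and 26 weeks. All five matrices are collected at each: "At T1 and T2, follow-up assessments will include the administration of primary and secondary outcome measures as well as biological sample collection". Table 1 places the baseline samples in the week 2 column, the program in weeks 3-12 and T1 at week 12.

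Sample Types and Collection Procedures: for nails, "Participants will clip the distal ends of their fingernails at home before the assessment visit". Hair is cut at the scalp and specified by strand diameter or by mass, without a length. It adds: "The root end will be marked with a hair tie".

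Sample Processing Protocols: nails are washed, "then dried and mechanically ground using a ball mill to produce a homogeneous powder suitable for downstream analysis". For hair, "Hair samples will undergo solvent-based washing to remove surface contamination, followed by drying and mechanical pulverization using a ball mill". No segment cut is mentioned.

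Statistical Analysis says that metabolomic variables are analyzed at every time point. Under Metabolomics, partial least squares and multiple regression are to "model associations between metabolite profiles, their changes over time, and changes in depressive symptoms". No lag or matrix-specific time window is given in either place.

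**The concern.** Plasma, urine and saliva describe the body at about the time of collection. A distal nail clipping describes it when that piece of nail was formed. If that was before baseline for both the T0 and T1 clippings, their difference contains no treatment period. The HDRS-17 change between the same two visits does. Regressing one on the other links quantities from different calendar windows.

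The study's second component is a search for metabolic signatures of treatment response. A null nail result at T1 could be taken as no biomarker change when none could yet have appeared. An association, if found, would be assigned to the wrong period. More participants would not help, because the problem is timing and not precision.

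Hair raises a related question. If whole strands are milled, the period that a sample covers depends on each woman's hair length.

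**Working it through.** The protocol gives no formation window to reproduce. Its one computed figure, the sample size (96, inflated to 120), reproduces (power 0.902 at N=96; 96/0.80 = 120) and does not bear on this point.

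**Inputs from the protocol.** T1 is 12 weeks and T2 26 weeks after baseline. Because Table 1 puts baseline samples at week 2, the gaps from the T0 sample are 10-12 weeks to T1 and 24-26 weeks to T2.

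**Assumptions, not in the protocol.** Nail growth 2.5, 3.0, 3.5 or 4.0 mm/month; length from the growth zone to the cutting line 10, 12, 14 or 16 mm; clipping 2 mm long. Hair growth 0.8-1.25 cm/month. One month is 4.348 weeks.

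**Nails.** Lag in weeks = length / rate × 4.348.
- Shortest: 10 / 4.0 × 4.348 = 10.9 weeks.
- Longest: 16 / 2.5 × 4.348 = 27.8 weeks.
- The newest part of a clipping formed at (gap − lag) weeks relative to T0. The tip is older by 2 / rate × 4.348 weeks.

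Four rates, four lengths and two gaps give 32 scenarios.

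| Clipping | Wholly before T0 | Mixed | Wholly after T0 |
|---|---|---|---|
| T1 | 31 | 1 (48% before T0) | 0 |
| T2 | 3 | 4 (3-72% before T0) | 25 |

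- T1, mid-range (3 mm/month, 12-14 mm, 12-week gap): formed about 5 to 11 weeks before T0.
- T1, the single exception (4.0 mm/month, 10 mm, 12-week gap): formed from week −1.0 to week +1.1. Counting Table 1's weeks from baseline, that is still before the program starts in week 3.
- Break-even: 12 weeks is 12 / 4.348 = 2.76 months. For a T1 clipping to be wholly post-baseline even with a 10 mm length, growth must reach (10 + 2) / 2.76 = 4.3 mm/month, above the assumed range.
- T2: most clippings fall within the program weeks. At the slow end some are still pre-baseline. At the fastest rate and shortest length they formed just after the program (weeks 11.0-13.1 or 13.0-15.1 after T0, for the 10- and 12-week gaps).

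**Hair, only if whole strands are milled.** Growth from T0 to T1 = rate × gap / 4.348.
- Low: 0.8 × 10 / 4.348 = 1.8 cm.
- High: 1.25 × 12 / 4.348 = 3.4 cm.
- Pre-baseline share at T1 = 1 − growth / strand length, with a floor of zero.

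| Strand | Pre-baseline share at T1 |
|---|---|
| 2 cm | 0-8% |
| 4 cm | 14-54% |
| 6 cm | 43-69% |
| 10 cm | 66-82% |
| 20 cm | 83-91% |

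The share passes one half only for strands longer than about 3.7-6.9 cm (twice the growth).

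**The case against.** The strongest reply is that the biomarker work is labeled exploratory, hypothesis-generating and not powered, and that the metabolomics section names no interval. It does not explicitly pair the T0-T1 nail change with the T0-T1 HDRS-17 change, so a T0-T2 or lagged use remains open. T0 nails that record pre-treatment exposure also suit a search for predictors of response. All of this is fair, and it limits the point. It does not remove it: metabolites are to be analyzed at all time points and their changes related to symptom changes with no lag, so the T0-T1 nail contrast falls within the plan as written. An exploratory label does not make an exposure window overlap the period being explored. The limitations paragraph in the Discussion covers home collection and circadian timing, not formation lag.

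Three stronger readings go beyond the documents.
- A reader might infer that hair is milled unsegmented and that T1 hair is mostly pre-baseline. The article is only silent on segmentation, it marks the root end, and it refers to operating procedures not shown here. Even for whole strands, mostly pre-baseline fails for short hair, which the collection procedure provides for.
- A reader might infer that nail or hair changes can never be matched to treatment. T2 nails mostly cover the program weeks, and a short proximal hair segment could cover T0-T1.
- A reader might infer that the trial's efficacy result is at risk. It does not use these samples.

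**Conclusion.** The point holds for the T0-T1 nail contrast. Under the assumed growth rates and lengths, both clippings are essentially pre-treatment, so their difference cannot reflect the program, whereas the HDRS-17 change over the same visits can. The conclusion depends on growth figures that the protocol does not supply, but it is stable across nearly all of the range tried. For hair the point is conditional: the window is unstated, and it matters only if long strands are milled whole. The consequence is confined to the nail and hair parts of the exploratory metabolomics substudy.

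**What to change.** 1. In the metabolomics analysis, state the time window that each matrix represents. Do not relate the T0-T1 nail change to the concurrent HDRS-17 change.
2. Treat T0 and T1 nails as pre-treatment exposure, usable as predictors. Use the T2 nail sample as the one that mostly overlaps the intervention, with its lag stated as an assumption and varied over a range, since at slow growth it may still be partly or wholly pre-baseline.
3. For hair, confirm that a fixed proximal segment from the marked root end is analyzed, with the same length at every visit and no longer than the expected growth over the 10-12 week gap (about 1.8-3.4 cm under the assumed rates). A length near the lower end is safe across that range.
4. Keep same-visit change analyses for plasma, urine and saliva as planned.

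The cost is a few sentences in the analysis section and one line in the hair procedure, with no new visits or samples. There is time: 8 participants were enrolled as of April 2026, analysis has not begun, and all samples are to be assayed in one run after collection ends. The price is losing the nail T0-T1 change analysis and having less hair mass per sample, which the laboratory should confirm is enough for the assay.
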